## Abstract

**Background:**

Sleep problems are highly prevalent in people with dementia. Nevertheless, there is no “gold standard” intervention to prevent or reduce sleep problems in people with dementia. Existing interventions are characterized by a pronounced heterogeneity as well as insufficient knowledge about the possibilities and challenges of implementation. The aim of this study is to pilot and evaluate the effectiveness of a newly developed complex intervention to prevent and reduce sleep problems in people with dementia living in nursing homes.

**Methods:**

This study is a parallel group cluster-randomized controlled trial. The intervention consists of six components: (1) the assessment of established sleep-promoting interventions and an appropriate environment in the participating nursing homes, (2) the implementation of two “sleep nurses” as change agents per nursing home, (3) a basic education course for nursing staff: “Sleep problems in dementia”, (4) an advanced education course for nursing staff: “Tailored problem-solving” (two workshops), (5) workshops: “Development of an institutional sleep-promoting concept” (two workshops with nursing management and sleep nurses) and (6) written information and education material (e.g. brochure and “One Minute Wonder” poster). The intervention will be performed over a period of 16 weeks and compared with usual care in the control group.

Overall, 24 nursing homes in North, East and West Germany will be included and randomized in a 1:1 ratio. The primary outcome is the prevalence of sleep problems in people with dementia living in nursing homes. Secondary outcomes are quality of life, quality of sleep, daytime sleepiness and agitated behavior of people with dementia, as well as safety parameters like psychotropic medication, falls and physical restraints. The outcomes will be assessed using a mix of instruments based on self- and proxy-rating. A cost analysis and a process evaluation will be performed in conjunction with the study.

**Conclusions:**

It is expected that the intervention will reduce the prevalence of sleep problems in people with dementia, thus not only improving the quality of life for people with dementia, but also relieving the burden on nursing staff caused by sleep problems.

**Trial registration:**

Current controlled trials: ISRCTN36015309. Date of registration: 06/11/2020.

## Background

Due to demographic change, the population of older people will continue to increase. It is expected that by 2050 the number will double from 1 to 1.5 million to around 3 million [1]. With increasing age, the prevalence of dementia increases. In Germany, prevalence rates for people aged ≥65 `s have been estimated at 8.8% and the annual incidence at 1.9% [2, 3]. Dementia is a clinical syndrome characterized by cognitive, neuropsychiatric and functional symptoms. It involves difficulties in memory, disturbances in language, psychological and psychiatric changes as well as impairments in activities of daily living [4].

People with dementia have increased sleep problems, which could be defined as a decreased total sleep time of one quarter of the individual total nocturnal sleep appertaining to their premorbid nocturnal sleep pattern or, if this is not known, a sleep pattern of less than six hours between 9:00 pm and 6:00 am [5]. The main reasons for sleep problems are advancing age, chronic illnesses, mobility restrictions, reduced brain performance and taking medication [6–9].

A German study showed a 23%prevalence of sleep disturbances for people with dementia living in nursing homes [10], and a recent meta-analysis demonstrated a 20% prevalence in validated proxy-based questionnaires and a prevalence of 38% for any symptom of sleep disturbances [11].

Evidence demonstrates that poor sleep quality is associated with harmful consequences regarding physical health, mental health disorders and quality of life [12, 13]. Sleep problems in people with dementia are often accompanied by agitation or aggressive behavior [14] and are associated with significant caregiver distress [15]. In nursing home care, the relationship between nurses and people with dementia results in a reciprocal interaction. The behavior and emotions of people with dementia affect nurses’ well-being and behavior, and vice versa [16]. This means that residents’ challenging behaviors lead to a lower quality of general health, reduced workability, high burnout levels [17], depression, anxiety and sleep problems for the nursing home staff [18]. As a consequence, this can result in higher staff sick leave and turnover, and increased costs [19].

To counteract challenging behavior, nursing home residents are often prescribed psychoactive drugs, including hypnotics. A study from the USA found that 47% of people with dementia in nursing homes received psychotropic medication [20]. The use of benzodiazepines and non-benzodiazepines is associated with an increased rate of falls and the associated increased risk of fractures [21, 22]. A Cochrane review showed that there are currently no effective pharmacological interventions to treat sleep problems in people with dementia in various settings [23]. Although regularly prescribed, drug therapies with, for example, antipsychotics, benzodiazepines or z-drugs are of unclear effectiveness and potential harm and therefore not considered to be the first choice for sleep disturbances in people with dementia in nursing homes [23].

In a Cochrane review currently being prepared on non-pharmacological interventions [24], multi-component or “complex” interventions, with contain multiple (interacting) components, are shown to have the strongest potential of being effective for improving sleep. The main challenge of interventions aiming to prevent or reduce sleep disturbances are the number of potential triggers or causes of sleep disturbances, the number and difficulty of behaviors and skills required by those delivering the intervention, the number of groups of organizational levels targeted by the intervention, the number and heterogeneity of outcomes, and the degree of flexibility or tailoring of the intervention [25, 26]. Based on these, complex interventions appear to be most appropriate for the multifactorial origin of sleep disturbances and the requirements for a tailored intervention.

In a recent systematic review [27], we described and summarized non-pharmacological complex interventions targeting sleep problems in nursing home residents. Frequently used components of complex interventions aiming to reduce sleep problems were: activating nursing home residents during daytime, creating bedtime routines, creating sleep-promoting night care, avoiding negative symptoms such as pain, itching, anxiety, and/or creating a sleep-promoting environment (e.g. concerning light, noise, temperature). Identified complex interventions showed a wide variance regarding the addressed influencing factors for sleep problems, the intervention components applied, and the intensity and duration of delivery. Therefore, we were not able to recommend one specific component of an intervention, but a whole bundle. However, the review recommends the rigorous development of non-pharmacological interventions to improve residents’ sleep in nursing homes, taking the potential barriers for implementation into consideration.

## Objectives

The aim of this trial is the piloting and evaluation of the effects of a newly developed complex intervention program to prevent and reduce sleep disturbances in people with dementia in nursing homes. The intervention was developed according to the UK Medical Research Council (MRC) framework for complex interventions [25] and is based on the results from an own systematic review [27], a theory of change [28] and a survey [10, 15] as well as qualitative interviews, observations and additional literature. This new complex intervention will be evaluated in an exploratory mixed-methods cluster-randomized controlled trial. Implementation fidelity as well as the promoting and inhibiting factors of the intervention’s implementation will be examined in an accompanying process evaluation [29, 30]. In addition, an evaluation of the implementation costs will be carried out.

## Study design

The MoNoPol-Sleep (multi-modal, non-pharmacological intervention for sleep disturbances in people with dementia living in nursing homes) trial is a cluster-randomized controlled trial with two parallel groups and a 16-week follow-up. A total of 24 nursing homes will be randomized either to (1) an intervention group receiving the complex intervention program or to (2) a control group receiving usual care (see Fig. 1). The expected start of recruitment for the study participants is March 2021.

**Fig. 1 Fig1:**
[figure not shown]
Flowchart for the cluster-randomized controlled trial

## Methods: participants, interventions and outcomes

### Eligibility criteria

#### Cluster level

Nursing homes must have at least 50 residents to be included. Moreover, nursing homes must indicate that they have sufficient resources (staff and time) to conduct the study and to implement the intervention, and that no parallel dementia-specific care-related project is being conducted there during the MoNoPol-Sleep trial.

#### Resident level

The inclusion criteria for people with dementia living in nursing homes are a documented dementia diagnosis or a score of ≥3 on the Dementia Screening Scale (DSS) [31]. Further criteria are the presence of at least two sleep problems according to the Sleep Disorder Inventory (SDI) [32] and a length of stay ≥2 weeks in the respective cluster. Exclusion criteria are documented sleep apnea, REM-sleep-behavior disorders or respite care.

#### Nurse level

The following inclusion criteria for nurses will be applied: a contract for at least part-time (half-a-day) work and at least three night shifts during the last 3 months prior to data collection.

### Recruitment of clusters and study participants

Nursing homes will be recruited in the catchment regions of Lübeck (Northern Germany), Halle an der Saale (Eastern Germany) and Witten (Western Germany). Eight clusters per region will be included in the convenience sample. For the recruitment, each study center (Lübeck, Halle an der Saale, Witten) will use existing contacts to nursing homes in their area. In addition, nursing homes will be recruited by means of an information folder, announcements in relevant journals for long-term care in Germany, and the study website (www.monopol-sleep.de).

Nursing homes interested in participating in the study will be contacted by the study center via telephone or E-Mail and verbally informed about the study in a telephone call or during a personal visit. The aims and contents of the MoNoPol-Sleep study will be presented to the respective nursing home manager, who will decide whether to participate.

#### Who will take informed consent?

One staff member in each nursing home will be deployed as the project coordinator. Interested and eligible people with dementia and/or their legal representative will receive written study information provided by the project coordinators. Informed consent will be obtained by the project coordinators and sent to the respective study center.

### Intervention

The aim of the intervention is to prevent and reduce sleep problems of people with dementia by implementing person-centered care including a sleep-promoting care environment for each cluster.

#### Intervention description

##### Intervention group

The intervention consists of six components, which will be implemented over a period of 16 weeks with the support of the research team (Fig. 2). The six components are described in detail in Table 1.

**Fig. 2 Fig2:**
[figure not shown]
Schedule of the MoNoPol-Sleep intervention components

**Table 1 Tab1:** Detailed description of the components of the MoNoPol-Sleep intervention to reduce and prevent sleep problems for people with dementia in nursing homes

No.	What? Procedures	Why? Rationale and theory	What? Materials	How? Modes of delivery	Who? Intervention provider	When and how much? Number of sessions etc.
1.	**Assessment of established sleep-promoting interventions and an appropriate environment in the participating nursing homes** ▪ This assessment is based on interviews with the nursing staff (from night shifts) and a proxy assessment (via structured observations) of implemented interventions to promote the sleep of people with dementia.	▪ Nursing homes are heterogeneous in terms of the existing prevalence of sleep problems and implemented interventions to avoid or reduce sleep problems [10, 33]. ▪ To ensure that the MoNoPol-Sleep intervention can be individually tailored to the needs of the participating nursing home, an assessment will be carried out.	▪ Self-developed structured observation checklist and interview guide (which was already tested and adapted during the intervention development) ▪ Structured feedback as part of intervention component No. 3	▪ Observation on site (participating nursing home) and face to face interviews	▪ Research staff	▪ One proxy assessment (on site observation between 5 p.m. and 2 a.m.) and interviews with a minimum of four nurses (two day shift and two night shift) ▪ First week of the intervention phase
2.	**Implementation of two “sleep nurses” as change agents per nursing home.** ▪ During the intervention phase, the sleep nurses (one nurse from the day shift and one nurse from the night shift) act as contact persons, multipliers, coordinators, change agents and as implementers of person-centered sleep promotion. ▪ For this purpose, the sleep nurses receive in-depth knowledge about sleep promotion, implementation strategies with regard to the MoNoPol-Sleep interventions and problem-solving strategies. ▪ In addition, the sleep nurses can reflect on their actions in coaching sessions and develop new problem-solving strategies.	▪ Local praxis development champions are a crucial factor to implement person-centered care interventions [34, 35] ▪ Sleep nurses are important as contact persons, change agents and local champions. Such champions are recommended for the implementation of complex interventions [36].	▪ Written education material ▪ Written profile of the sleep nurses	▪ Education sessions (both sleep nurses together for each nursing home) ▪ Coaching sessions (both sleep nurses together for each nursing home)	▪ Research staff	▪ Education: approx. Two hours of education as part of component No. 3 ▪ Coaching: approx. One hour after each workshop of the components No. 4 and 5
3.	**Basic education course for nursing staff: “Sleep problems in dementia”.** ▪ The education session is divided into three parts: ▪ Part 1 aims to provide information on the following topics: information on the background, course, schedule and responsibilities of the MoNoPol-Sleep trial, principles of person-centered care, sleep and sleep problems of people with dementia. Moreover, evidence-based information regarding six strategies to promote sleep of people with dementia will be presented. These strategies are: (1) Activation of people with dementia during the day, (2) Review and, if necessary, adjustment of the “going to bed routine”, (3) Review and, if necessary, adjustment of the night care (e.g. change of position routine), (4) Freedom from symptoms (e.g. with regard to thirst, pain, itching, anxiety), (5) Reflection of the appropriateness of sleep medication (6) Review and, if necessary, adjustment of the sleeping environment (e.g. light, sounds, temperature) ▪ The results of the assessment of established sleep-promoting interventions (component No. 1) will be presented in Part 2. ▪ Part 3 aims to provide information on the function and tasks of the new role of a sleep nurse (component No. 2) as change agent in each nursing home (intervention group).	▪ Information regarding six strategies to promote sleep of people with dementia will be based on three reviews [23, 27, 37]. ▪ To give the nursing staff basic information about sleep problems in dementia as well as the schedule of the upcoming interventions. ▪ Sleep nurses need further information to fulfill their new role.	▪ Written education material ▪ Information brochure (component No. 6)	▪ Group session	▪ Research staff	▪ One session divided into three parts: ▪ Part 1 takes approx. 45 min, while Part 2 takes approx. 45 min and Part 3 lasts approx. Two hours ▪ Second week of intervention
4.	**Advanced education course for nursing staff: “Tailored problem solving” (two workshops).** ▪ Two workshops which aim to support the implementation of person-centered sleep promotion and problem-solving competencies. ▪ In both workshops, one case of a resident with sleep problems from the facility will be discussed and solutions for improved sleep promotion sought. ▪ Each workshop contains the following seven steps: (1) Introduction, (2) Presentation of one resident as a case with sleep problems by the sleep nurse, (3) Prioritizing of care problems by all workshop participants, (4) Information about potential reasons for sleep problems by the moderating researcher, (5) Analysis of potential influencing factors for case-specific sleep problems by all workshop participants, (6) Formation of hypotheses for understanding, (7) Development and consensus on an action plan.	▪ Based on a theory of change which was developed during the MoNoPol-Sleep intervention development: Sleep problems and their causes are individual for each person with dementia. ▪ Nursing home staff needs support in problem solving which take the available resources of people with dementia and the care environment into account. ▪ The seven steps of the workshop are based on the available knowledge for conducting case conferences [38–40].	▪ Direction plan for the workshop ▪ Digital presentation ▪ Written education material ▪ Self-developed, standardized case analysis chart ▪ Moderator manual including e.g. list of causes for sleep problems, list of symptoms of sleep problems)	▪ Group sessions	▪ Research staff ▪ Sleep nurses	▪ Both workshops take approx. 1.5 h each ▪ The first workshop will be held after component No. 3 and by the 6th week of intervention at the latest ▪ The second workshop will be held between the 7th and 12th week of intervention
5.	**Workshops: “Development of an institutional sleep-promoting concept” (two workshops with nursing management and sleep nurses).** ▪ Two workshops aimed at the development and implementation of an organizational, specific action plan to promote sleep. ▪ The first workshop contains the following four steps: (1) Introduction, (2) Knowledge refreshment regarding the results of the assessment of established sleep-promoting interventions (component No. 1) and six strategies to promote sleep of people with dementia (see component No. 3), (3) Identification of organizational structures and processes which promote or hinder the sleep promotion, (4) Development and consensus on an action plan. ▪ The second workshop contains three steps: (1) Introduction, (2) Identification of organizational structures and processes which promote or hinder the implementation of the action plan (workshop 1), (3) Development and consensus on the implementation of the action plan.	▪ Based on a theory of change which was developed during the MoNoPol-Sleep intervention development: Nursing homes are heterogeneous in terms of opportunities to provide person-centered sleep promotion.	▪ Self-developed, standardized workshop protocol including resources for the moderator (e.g. action plan form)	▪ Group sessions	▪ Research staff ▪ Sleep nurses	▪ Both workshops take approx. 2.5 h each ▪ The first workshop will be held after component No. 3 and by the 6th week of intervention at the latest ▪ The second workshop will be held between the 7th and 12th week of intervention
6.	**Written information and education material (e.g. brochure and “One Minute Wonder” poster).** ▪ A series of eight “One Minute Wonder” posters addressing restful sleep, the identification of sleep problems and six strategies to promote sleep of people with dementia (see component No. 3). ▪ Two individual nursing home “One Minute Wonder” posters which will contain the nursing home’s specific action plan and its implementation (component No. 5). ▪ Information brochure which contains evidence-based information on sleep and sleep problems of people with dementia, six strategies to promote sleep of people with dementia (see component No. 3) and education material.	▪ See components No. 1 to 5	▪ “One Minute Wonder” poster ▪ Information brochure	▪ Not applicable	▪ Research staff	▪ Each ward of the participating nursing homes will receive the poster in weekly rhythm ▪ The first posters of the series are distributed on the wards after the basic education course (component No. 3) ▪ After completion of the basic education course, the staff of the nursing home will receive a brochure

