### Outcomes

To investigate the intervention effects, quantitative measurements will be used to measure variables regarding people with dementia and nursing staff. Table 2 summarizes all the outcome instruments.

**Table 2 Tab2:** Outcome instruments

People with dementia				
Variable	Instrument	Source	Measurement points	Type of variable
Demographic variables (e.g. documented sleep apnea, documented dementia diagnosis, Dementia Screening Scale, length of stay in nursing home)	Single items	Nursing records	T0	Inclusion and exclusion criteria
Demographic Variables (e.g. age, sex, care dependency level^a^)	Single items	Nursing records	T0	Control variables
Sleep Disorders	Sleep Disorder Inventory [32]	Retrospective rating by registered nurse (night shift)^c^	T0, T1, T2	Primary outcome, Inclusion criterion
Objective Sleep Measures^b^	Algorithm to analyze actigraphic data with respect to sleep patterns [41, 42]	Actigraphy	T0, T2	Secondary outcome
Quality of Sleep	Pittsburgh Sleep Quality Index [43]	Self-rating by participating people with dementia^d^	T0, T2	Secondary outcome
Daytime Sleepiness	Essener Questionaire of Age and Sleepiness in the Elderly (EFAS) [44]	Retrospective rating by registered nurse (day shift)	T0, T2	Secondary outcome
Quality of Life	QUALIDEM 2.0 [45, 46]	Retrospective rating by registered nurse (night shift)^c^	T0, T2	Secondary outcome
Agitation	Cohen-Mansfield Agitation Inventory [47]	Retrospective rating by registered nurse (day shift)^b^	T0, T2	Secondary outcome
Accidental falls	Single item	Nursing documentation	T1, T2	Control variable
Physical restraint use	Single item	Nursing documentation	T1, T2	Control variable
Psychotropic medication	Single items	Nursing documentation	T1, T2	Control variable

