Quality of life of people with dementia (secondary endpoint) will be assessed using the German version of the QUALIDEM 2.0 [45, 46]. The QUALIDEM 2.0 consists of two successive versions for mild to severe (37 items) and very severe dementia (18 items). Based on the instrument items, subscale values will be determined for the dimensions “Care relationship”, “Positive affect”, “Negative affect”, “Restless, tense behavior”, “Social relationships”, “Social isolation”, “Positive self-image”, “Feeling at home” and “Something to do” retrospectively for the last weeks [46, 55]. The latter three subscales will be omitted for people with very severe dementia. Higher subscale values correspond to a higher quality of life.

Agitated behavior of people with dementia will be recorded retrospectively for the last 2 weeks, using the German version of the Cohen Mansfield Agitation Inventory (CMAI) [56, 57]. The CMAI consists of 29 items, each rated on a 7-point scale of frequency of occurrence of agitated behaviors (proxy-based) and a 5-point scale of how disturbing the behavior is. These are recorded in terms of their frequency, their caused burden for nurses and for the people with dementia themselves. The total score ranges from 29 to 203 for frequency and 29 to 145 for burden for nurses. Higher values correspond to an increasing frequency of burden caused by agitated behavior [56, 57].

Sociodemographic data such as age, sex and care dependency level as well as data regarding accidental falls, the use of physical restraints and psychotropic medication (N05C, N05A, N05B, N06A) will be recorded from the available care documentation or based on self-developed forms with proven validity in previous studies [48, 58].

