#### Adverse event reporting and harms

Given the nature of the intervention, we do not expect serious adverse events. Thus, no interim analysis is planned and no termination rules will be applied.

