## Discussion

This cluster-randomized controlled trial will investigate the effectiveness of a complex intervention to avoid and reduce sleep problems in people with dementia living in nursing homes. We do not assume negative effects for the study participants. We expect a significant reduction of sleep problems of the participating people with dementia when compared to the control group. We also expect that the process evaluation results of this study will enrich our knowledge of promoting factors and obstacles to the implementation of this complex intervention. If implemented successfully, the updated program will comprise a less extensive and potentially less costly intervention to avoid and reduce sleep problems in people with dementia. The comprehensive assessment of process measures and the cost analysis can increase the knowledge base for the further development of the intervention. During the study, the German version of the PSQI as well as the SDI will be investigated regarding their psychometric properties (reliability and validity), which will provide important insights into the use of these instruments for the German versions.

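### Night-time repositioning is a named target for review and adjustment, but no variable collected in both arms would register skin harm

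*Protocol article*

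**What the plan says.** **Intervention.** Table 1, component 3 (basic education course) gives as its third strategy "Review and, if necessary, adjustment of the night care (e.g. change of position routine". The strategy goes beyond the course. In component 5 the first management workshop goes back over the "six strategies to promote sleep of people with dementia (see component No. 3), (3) Identification of organizational structures" before the home agrees its action plan, and component 6 puts the six strategies into the posters and the brochure.

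**Harm-related variables.** The abstract (Methods) speaks of "safety parameters like psychotropic medication, falls and physical restraints". The Outcomes section says "Table 2 summarizes all the outcome instruments". That table has rows for accidental falls, physical restraint use and psychotropic medication, taken from nursing documentation at T1 and T2 and typed as control variables. The text on secondary outcomes for people with dementia agrees: "data regarding accidental falls, the use of physical restraints and psychotropic medication (N05C, N05A, N05B, N06A) will be recorded".

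**Adverse events.** The section on adverse event reporting and harms reads "Given the nature of the intervention, we do not expect serious adverse events", and adds that "no termination rules will be applied". It describes no collection procedure. The section on communicating amendments says that the ethics committee is told of serious or unexpected events. The Discussion states: "We do not assume negative effects for the study participants".

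**The concern.** When a programme opens a care routine to change, its harm measures should cover the physical risk that the routine exists to control. Repositioning protects skin. If a home alters the night routine for a dependent resident, a pressure ulcer is the foreseeable adverse result, and no listed variable would pick it up.

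The gap matters because the primary outcome is sleep problems rated by night nurses on the Sleep Disorder Inventory. Fewer care disturbances at night could improve that rating while a cost to the skin went unseen. The trial is exploratory and looks ahead to a fully powered one, so a harm signal not collected now cannot inform the later design.

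**Working it through.** No figure in the plan bears directly on this point, so the main check sets the sections side by side.

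**1. Is repositioning a target of change?** Yes. It is the named example in the third strategy (Table 1, component 3), and the six strategies are carried into the action plan and the materials (components 5 and 6).

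**2. Does any variable collected in both arms register skin harm?**

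| Source | What it captures | Skin harm? |
|---|---|---|
| Table 2, nursing documentation, T1 and T2 | falls, restraints, psychotropic medication | no |
| Table 2, rating scales and actigraphy | sleep, sleepiness, quality of life, agitation, nurse distress | no |
| Secondary-outcome text | the same three record items plus sociodemographic data | no |
| Adverse event section | an expectation only, no procedure | no |
| Ethics committee notification | serious or unexpected events, no method of finding them | only if noticed and judged to qualify |
| Table 3, process evaluation, T2 | care-plan documents (5 residents per cluster), observed performance of care plans, interviews (4 per cluster) | indirectly, intervention arm only |

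The care-plan analysis covers 12 intervention clusters × 5 = 60 of a planned 12 × 15 = 180 residents, with no control counterpart. It may show that a routine changed. It cannot show whether skin harm differed by arm.

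**3. How precise would an added item be?** The design inputs are 12 clusters of 15 per arm, an intra-cluster correlation of 0.05, and 80% versus 61% at two-sided 5%.

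- Design effect = 1 + (15 − 1) × 0.05 = 1.70. Effective size = 180 / 1.70 = 105.9 per arm. Power for the primary comparison is 86.3% (stated 85%).
- With 10% dropout the cluster size is 13.5, the design effect 1 + 12.5 × 0.05 = 1.625, and the effective size 162 / 1.625 = 99.7. Power is 84.2% (stated 84%).

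The stated design figures reproduce, so these effective sizes can be carried over. No skin-harm rate is given, so I use a bound that needs none. If no event at all were seen in an arm, the one-sided 95% upper limit for the true rate is 1 − 0.05^(1/n):

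- n = 105.9: 1 − 0.05^(1/105.9) = 2.8%
- n = 99.7: 1 − 0.05^(1/99.7) = 3.0%

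This assumes that the correlation planned for the sleep outcome also holds for skin harm, which the documents do not say. Even an arm with no events would leave a true rate of nearly 3% open, so the item supports description and not a test.

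**The case against.** **The wording gives no direction.** The strategy is a review, with adjustment only if necessary. A home could individualise or increase repositioning, and the section on concomitant care says the programme replaces no part of health care. This stands. A reader might infer that homes are asked to reposition less, and the text does not support that. The point needs only that the routine may change.

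**The Discussion states an expectation.** A reader might infer that the protocol declares the programme harmless, or that the trial will be reported as such. Neither is written. Other negative effects can be examined through falls, restraints, psychotropic use and agitation, so only skin harm is left out. Nor is it shown that this is the only strategy without a matching measure.

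**Severe events have a route.** Serious or unexpected events go to the ethics committee, so it would be wrong to say that no pressure ulcer could ever come to light. But no ascertainment in both arms is described, and a non-serious ulcer would not clearly qualify.

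**The exposed group is unknown.** The protocol does not say how many residents are repositioned at night. Three of the seven sleep items involve getting up, walking about or dressing, so many participants may be mobile. This stands, and it is a reason to give no expected event count.

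**The article is condensed.** A fuller harms form may exist, and the abstract's safety list is open-ended. This carries less weight, because the article presents Table 2 as covering all outcome instruments and has its own harms section, which rests on an expectation.

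**Conclusion.** The point holds in a limited form. Night-time repositioning is a named subject of review and possible adjustment, the three harm-related variables collected in both arms would not register skin harm, and no systematic adverse event ascertainment is described. The expectation of no negative effects therefore cannot be examined for this one harm.

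The gap is one absent item for a planned 360 residents. How many events go unseen cannot be derived, because the documents give neither a pressure-ulcer rate nor the share of residents repositioned at night. The conclusion rests on reading Table 2 as the complete outcome list, as the article presents it. It is a cheap improvement to what the trial can say about safety. It corrects no false statement or figure, and it is no evidence that the programme harms.

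**What to change.** Add one yes/no item, new or worsened pressure ulcer since the last visit, to the nursing-documentation extraction at T1 and T2 in both arms, and record presence at T0. Add the row to Table 2, list it with the safety parameters, and report it descriptively by arm. No formal between-arm test should be relied on.

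The cost is one line on the case report form in an extraction already done at T1 and T2, one baseline entry, and a few minutes per resident. There are two drawbacks. The data are only as good as each home's documentation, which could differ between arms if attention to night care changes. Precision is also low. The change concerns measurement alone and proposes no repositioning rule.
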